**Figure 1 figure1:**
[figure not shown]
Study timeline.

### Intervention

The intervention will involve sending text messages and providing brief, individualized, web-based feedback sessions based on the eating behavior assessments completed during the study. The text messages will be distributed on 2 nonconsecutive days per week, that is, Tuesdays and Fridays, through the General Data Protection Regulation–compliant app *m-Path* [35] (the same app will be used for implementing the evaluations; refer to the next section, *Measurements*). An in-person meeting with each of the participants will be set on their first day in the study to help them install the app on their mobile phones and provide training if needed. The text messages will contain brief educational messages about human health and the environmental and socioeconomic effects of dietary choices; motivational messages to encourage the adoption of sustainable healthy diets by participants, providing tips to achieve their own objectives; or links to recipes, providing ideas on tasty sustainable healthy meals. These text messages were developed based on a previous attempt to identify relevant behavior change techniques for changing eating behaviors [14] and the compendium of self-enactable techniques to change and self-manage motivation and behavior v1.0 [36].

The understandability and relevance of each message were pretested. Six individuals from our institution matching our inclusion criteria and not implicated in the development of this study were involved in testing and refining the messages. Initially, the messages were tested for comprehension and relevance. Participants rated how understandable each text message was on a scale of 1 to 10. They also had the possibility of commenting on these as well as suggesting improvements for each text message. After this, and based on end users’ suggestions, the text messages were reworded, refined, or even removed. Multimedia Appendix 3 shows the content of the final text messages and how they match specific behavior change techniques.

In addition to the text messages, individualized feedback will be provided via short web-based individual meetings (approximately 15 minutes) at the end of the baseline phase or beginning of the intervention phase and then every 6 weeks during the intervention, after 2 measurement weeks (Figure 1). During the web-based sessions, a member of the research team with extensive knowledge of sustainable healthy diets will review the assessments of the previous weeks with the participants; provide tailored advice to improve their diet with regard to its healthiness and sustainability; and answer any questions, doubts, or additional questions that they may have. No feedback session will be provided during the follow-up period.

### Measurements

Both quantitative and qualitative data will be collected (Table 1).

**Table 1 table1:** Summary table for the study’s objectives and their assessment.

Objective and assessment		Measurement
**1.1.a Changes in the environmental sustainability and healthiness of the diet**		
	Quantitative	Eating behaviors questionnaire
	Qualitative	Baseline interview: Dietary habits Healthy and sustainable diet Postintervention interview: Perceived effectiveness of the intervention
**1.1.b Changes in individual food groups and food waste**		
	Quantitative	Eating behaviors questionnaire
	Qualitative	Baseline interview: Dietary habits Healthy and sustainable diet Postintervention interview: Perceived effectiveness of the intervention
**1.2. Feasibility and implementation of the intervention**		
	Quantitative	Relevance of the interventional text messages
	Qualitative	Interview at baseline: Motivations and expectations from the study Interview after the intervention: Acceptability of the intervention Feasibility of the intervention Elements to improve Interview at the end of the study: Acceptability of the intervention
**2.1. Identifying potential mechanisms of action mediating the effect of the intervention on eating behaviors**		
	Quantitative	Mechanism of action questionnaire
	Qualitative	Interview at baseline: Motivations and expectations from the study Interview after the intervention: Perceived effectiveness of the intervention Feasibility of the intervention Elements to improve
**2.2. Identifying potential covariations and spillover effects among food groups and food composition and waste**		
	Quantitative	Eating behaviors questionnaire
**2.3. Potential interaction of socioeconomic status with the intervention effectiveness**		
	Quantitative	Eating behaviors questionnaire

### Quantitative Measurements

#### Questionnaires

Several self-reported questionnaires will be used to collect quantitative data. With the exception of the questionnaire collecting data about baseline characteristics, the questionnaires will be implemented through the study app (*m-Path*). These questionnaires will pop up as notifications in the app.

##### Baseline Characteristics

A baseline questionnaire will be used to collect descriptive data about the sociodemographic (ie, gender, age, education, household income, political orientation and postal code, number of people they live with, and if they usually cook for others), anthropometric (ie, height and weight), and health-related (ie, self-perceived physical and mental health, supplement intake, and smoking) characteristics of the participants, together with data about their general motivation for protecting the natural environment (Multimedia Appendix 4). It will be completed once at the inclusion through a Google form.

##### Eating Behaviors

As shown in Figure 1, eating behaviors will be assessed daily for 15 weeks through a brief questionnaire: participants will have to report their food intake at the end of each day during the 2 weeks of the baseline period; then, every 3 weeks during the intervention period; and afterward, once per month during the follow-up period, representing a total of 105 potential measurement days per participant spread over a year (15 evaluation weeks × 7 measurement days).

A 12-item questionnaire will assess the consumption of specific food groups relevant to environmentally sustainable healthy diets as well as food waste (Table 2) [25]. The present food frequency questionnaire was designed considering the need to minimize the total number of items and make it suitable for daily assessment while adding items about relevant food groups to assess food environmental sustainability and healthiness. For each food group, the number of servings consumed during the day will be asked. Specific foods gathered in the assessed food groups will be detailed, and their serving sizes will be provided with examples that the participants can easily interpret. For instance, a serving of vegetable is reported as a medium size dish of mixed salad, cooked vegetables, or vegetable purée—1 big tomato, 2 carrots, and 1 glass of gazpacho (Figure 2). The size of a serving was established based on the Spanish Society of Community Nutrition recommendations and other Spanish documents [37,38]. The exception will be whole grains and virgin olive oil, which will be assessed in terms of their proportion among all the grains and added fats consumed during the day, respectively. The reason for assessing them as a proportion is because of the priority of healthy fat and carbohydrate intake rather than the total amount of fat and carbohydrate consumed, as the recommended amount of total added fats and carbohydrates depends on the specific energy needs of each person.

Beyond food consumption, daily food waste will be measured with a “yes/no” binary question [39]. As, to our knowledge, there are no previous validated questionnaires to objectively assess the social aspect, changes in this specific sustainability dimension will not be quantitatively assessed but will be explored via the qualitative interviews. An extra open-question item will be added at the end of the 12-item questionnaire to give participants the opportunity to provide any comment or clarification if necessary. To ensure that they understand how their food consumption should be reported, participants will be explained at the initial meeting about the quantification of each food group and provided with an explanatory document showing how to respond to the questionnaire (Multimedia Appendix 5). Eventually, this will also be discussed in feedback sessions.

**Table 2 table2:** Items for evaluating food consumption and food waste.

Name and item			Answer options
**How many servings of the following food groups have you consumed today?**			
	Red or processed meat	(1) 0 servings, (2) 0.5 servings, (3) 1 serving, (4) 1.5 servings, (5) 2 servings, (6) 2.5 servings, (7) 3 servings, (8) 3.5 servings, (9) 4 servings, (10) 4.5 servings, (11) 5 servings, and (12) more than 5 servings	
	White meat, fish or eggs	(1) 0 servings, (2) 0.5 servings, (3) 1 serving, (4) 1.5 servings, (5) 2 servings, (6) 2.5 servings, (7) 3 servings, (8) 3.5 servings, (9) 4 servings, (10) 4.5 servings, (11) 5 servings, and (12) more than 5 servings	
	Dairy products	(1) 0 servings, (2) 0.5 servings, (3) 1 serving, (4) 1.5 servings, (5) 2 servings, (6) 2.5 servings, (7) 3 servings, (8) 3.5 servings, (9) 4 servings, (10) 4.5 servings, (11) 5 servings, and (12) more than 5 servings	
	Legumes	(1) 0 servings, (2) 0.5 servings, (3) 1 serving, (4) 1.5 servings, (5) 2 servings, (6) 2.5 servings, (7) 3 servings, (8) 3.5 servings, (9) 4 servings, (10) 4.5 servings, (11) 5 servings, and (12) more than 5 servings	
	Fruits or vegetables	(1) 0 servings, (2) 0.5 servings, (3) 1 serving, (4) 1.5 servings, (5) 2 servings, (6) 2.5 servings, (7) 3 servings, (8) 3.5 servings, (9) 4 servings, (10) 4.5 servings, (11) 5 servings, and (12) more than 5 servings	
	Nuts or seeds	(1) 0 servings, (2) 0.5 servings, (3) 1 serving, (4) 1.5 servings, (5) 2 servings, (6) 2.5 servings, (7) 3 servings, (8) 3.5 servings, (9) 4 servings, (10) 4.5 servings, (11) 5 servings, and (12) more than 5 servings	
	Sugary, salty and ultraprocessed foods	(1) 0 servings, (2) 0.5 servings, (3) 1 serving, (4) 1.5 servings, (5) 2 servings, (6) 2.5 servings, (7) 3 servings, (8) 3.5 servings, (9) 4 servings, (10) 4.5 servings, (11) 5 servings, and (12) more than 5 servings	
	Alcoholic drinks	(1) 0 servings, (2) 0.5 servings, (3) 1 serving, (4) 1.5 servings, (5) 2 servings, (6) 2.5 servings, (7) 3 servings, (8) 3.5 servings, (9) 4 servings, (10) 4.5 servings, (11) 5 servings, and (12) more than 5 servings	
	Sodas, juices, energy drinks, etc	(1) 0 servings, (2) 0.5 servings, (3) 1 serving, (4) 1.5 servings, (5) 2 servings, (6) 2.5 servings, (7) 3 servings, (8) 3.5 servings, (9) 4 servings, (10) 4.5 servings, (11) 5 servings, and (12) more than 5 servings	

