##### Eating Behavior Scoring Procedure

In terms of the scoring procedure, we designed an index for assessing dietary healthiness and environmental sustainability for every assessment week based on 10 out of the 12 items provided in Table 1. The item related to white meat, eggs, and fish is not considered in the score to avoid overrating protein groups. However, it will be used in the individual food analysis to assess whether, in the case of a reduction in the consumption of red and processed meat and not a simultaneous increase in legume consumption, red and processed meat is replaced by animal-based proteins (objective 2.2). The second item not included in the present index is the one assessing food waste. This last item will be used as a specific outcome in itself and is not included in our main score.

Therefore, the environmentally sustainable healthy diet score is computed from 10 items, each of which is treated continuously from 0 to 1 point; for example, the scoring of red and processed meat consumption is as follows: 0 points for the consumption of >2 servings of red and processed meat and 0.25, 0.5, 0.75, and 1 points for the consumption of 1.5, 1, 0.5, and 0 servings per week, respectively. Food consumption will be assessed as the average daily food consumed during the entire assessment week. The scoring criteria and rationales are listed in Table 3. The total score of the environmentally sustainable healthy diet index will be the sum of the points for each item. Thus, the environmentally sustainable healthy diet index will range from 0 to 10 points, with 0 points being the lowest score in terms of environmentally sustainable healthy diet and 10 points being the highest (best) score (Table 3). Our overall scoring criteria are based on the recommendations of reference entities in the field of nutrition, mainly the EAT-Lancet Commission, Food and Agriculture Organization, and World Health Organization [25,40,41].

**Table 3 table3:** Environmentally sustainable healthy diet index: scoring criteria.

Item	What does it assess?	Scoring criteria^a^	Rationale
Red and processed meat	Average daily red and processed meat consumption	1 point: 0 serv/w^b^ (or <0.15 serv/d^c^) 0 point: >2 serv/w (or >0.29 serv/d)	Ideally, no red or processed meat should be consumed in a sustainable healthy diet; however, up to 2 servings of red meat per week is acceptable [25].

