Dairy products	Average daily dairy product consumption	1 point: ≤1 serv/d 0 point: >2 serv/d	In a sustainable healthy diet, the optimal intake of dairy products should be at the lower end of the range 0 to 500 mL (milk equivalents) [25].
Legumes and soy	Average daily legume and soy product consumption	1 point: ≥1 serv/d 0 point: 0 serv/d	Plant-based proteins should be the main protein source in someone’s diet, for their own health and for that of the planet. At least 1 serving of legumes per day should be consumed in a sustainable healthy diet [25].
Fruits and vegetables	Average daily fruit and vegetable consumption	1 point: ≥5 serv/d 0 points: <1 serv/d	At least 5 servings of fruits and vegetable (in total) should be consumed per day [25]. Less than 1 serving per day will be scored as 0 points owing to their crucial daily consumption for a healthy diet.
Nuts (including peanuts)	Average daily nut consumption	1 point: 1-2 serv/d 0 point: 0 serv/d and ≥4 serv/d	Daily consumption of nuts is recommended owing to their health benefits. Indeed, they have been suggested even as a replacement for red meat. However, the quantity should be moderate, as some nut-tree crops are water, fertilizer, and pesticide intensive [15,25].
Sugary, salty, and ultraprocessed foods	Average daily sugary, salty, and ultraprocessed food consumption	1 point: 0 serv/w 0 point: >2 serv/w (or >0.29 serv/d)	These foods should be consumed as less as possible; ideally, they should be avoided or at least consumed no more than once a week [40].
Whole grains	Proportion of servings of whole grains in relation to the total servings of all grains	1 point: 100% whole grains 0 point: 0% whole grains	Whole grains should be prioritized over their refined versions [25].
Oils and fats	Proportion of servings of virgin or extra virgin olive oil in relation to the total added fat intake	1 point: 100% virgin or extra virgin olive oil 0 point: 0% virgin or extra virgin olive oil	Unsaturated and nonrefined oils, mainly virgin olive oil (extra or not) in our context, should be prioritized over other dietary fats [25].
Alcoholic drinks	Average daily alcoholic drink consumption	1 point: 0 serv/w 0 point: >2 serv/w (or >0.29 serv/d)	Ideally, no alcohol should be consumed. According to the World Health Organization, the impact of alcohol consumption on chronic and acute health outcomes is largely determined by the total volume of alcohol consumed [41].

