Other beverages: sodas, juices, energy drinks, etc	Average daily consumption of other unhealthy drinks	1 point: 0 serv/w 0 point: >2 serv/w (or >0.29 serv/d)	These foods should be consumed as less as possible; ideally, they should be avoided or at least consumed no more than once a week [40].

^a^Scores will range proportionally from 0 to 1 points. For instance, 0 points will be assigned for the consumption of >2 servings of red and processed meat per week and 1 point for 0 servings per week; 0.25, 0.5, and 0.75 points will be assigned for the consumption of 1.5, 1, and 0.5 servings per week, respectively.

^b^serv/w=servings per week.

^c^serv/d=servings per day.

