### Data Analyses

#### Sample Size and Power Analyses for the Quantitative Side of the Project

The sample size for this pilot study is constrained by financial and human resources. We plan to recruit a total of 21 participants, with 7 participants in each subjective socioeconomic group (refer to the *Participants* section). However, in terms of statistical power, we will benefit from the intensive longitudinal nature of the study, that is, 15 evaluation weeks and up to 105 daily observations per participant. For objective 1.1.a, for which a weekly environmentally sustainable healthy diet index will be used, up to 315 observations will be available in total (21 participants × 15 evaluation weeks) and 105 observations per socioeconomic group (7 participants × 15 evaluation weeks). For objective 1.1.b, for which the daily raw data will be used, up to 2205 observations will be available in total (21 participants × 105 daily assessments), 735 observations in the 3 socioeconomic groups (7 participants × 105 daily assessments), and 105 observations at the individual level (as a general rule of thumb, a minimum of 70 observations are required for conducting individual-level analyses [48]). Given the pilot nature of this trial, we conducted power simulation analyses only for objective 1.1.a (ie, change in the weekly level of food healthiness and environmental sustainability). Considering group-level analyses and the analytical strategy detailed in the next section and assuming an increase of 2 units in the environmentally sustainable healthy diet score per phase, simulated power analysis indicated an adequate power value of 96%. The simulation was performed by generating the response variable as follows:

Fixed effects: the intercept was set at 6, and the fixed coefficient for the phase was set as −2 for the initial phase and +2 for the final phase based on our average expected change in the main outcome.Random effects: it was assumed that each participant would have both a random slope and a random intercept and that both followed normal distributions, with SDs of 2 for the intercept and 0.5 for the slope. The correlation between them was set as 0.2. The random effect for each participant was created by drawing random numbers from a multivariate normal distribution whose covariance matrix was specified using these parameters (R mvrnorm from the package *MASS*).

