##### Objective 1.1.b: Changes in Individual Food Groups and Food Waste

An analytical strategy similar to that used for objective 1.1.a will be followed for testing the effect of the intervention on specific food groups, including red and processed meat, fruits and vegetables, ultraprocessed foods, and dairy products, and food waste. A linear mixed model similar to that performed for the first objective will be performed, but time will be expressed as measurement days instead of weeks, thus ranging from 1 to 105. In addition to the group and subgroup analyses performed for objective 1.1.a and maximizing the higher number of observations per participant within those outcomes, individual-level models will also be used to quantify the effect of the intervention on each participant separately from the others by following an idiographic approach.

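### The daily fruit and vegetable item stops at an open category just above 5 servings, the recommended level, so the objective 1.1.b effect on this outcome is attenuated as intake nears and passes 5 a day

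*Protocol article*

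**What the plan says.** Table 2 of the protocol article gives every serving-based food group the same daily answer list: half-serving steps from 0, ending in "11) 5 servings, and (12) more than 5 servings". For fruits and vegetables, Table 3 scores the weekly mean as "1 point: ≥5 serv/d 0 points: <1 serv/d". The Eating Behavior Scoring Procedure section says how the week is summarised: "Food consumption will be assessed as the average daily food consumed during the entire assessment week". The footnote to Table 3 adds that "Scores will range proportionally from 0 to 1 points".

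Fruits and vegetables is also one of the specific outcomes of objective 1.1.b. The sample size section says of it: "For objective 1.1.b, for which the daily raw data will be used". The Objective 1.1.b section of the data analysis says: "A linear mixed model similar to that performed for the first objective will be performed", with time counted in measurement days, and adds models fitted separately to each participant.

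The article states no numeric value for the open category. The daily questionnaire has a free-text comment, but no rule links it to that category.

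**The concern.** The recording ceiling coincides with the level Table 3 treats as the goal, and the intervention encourages fruit and vegetable consumption. A participant who moves from mixed days around 4 to mixed days around 5 or 6 places more and more days in the open category, where further increases are invisible. A linear model on those values understates the change, and understates it most in the participants who improve most from an already fair intake.

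That bears on three stated interests: the group effect on this outcome, the participant-by-participant models, and the comparison of rates of change between food groups described under Principal Findings. A recorded flattening near 5 could be read as a behavioural plateau when it comes from the answer list. The index deserves its own check, because the list truncates each day before averaging whereas Table 3 limits only the weekly mean.

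**Working it through.** **Scoring rule.** Inputs are the Table 3 anchors and its footnote. For red and processed meat, linear interpolation is 1 - x/2 with x in servings per week. At x = 1.5, 1 and 0.5 it gives 0.25, 0.5 and 0.75, which matches the article: "0.25, 0.5, and 0.75 points will be assigned for the consumption of 1.5, 1, and 0.5 servings per week, respectively". The same rule for fruits and vegetables is (weekly mean - 1)/4, limited to 0-1.

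**One week by hand.** True servings 7, 3, 7, 3, 7, 3, 5 sum to 35, so the mean is 5.00 and the item scores 1.00. With the three 7s replaced by the value of the open category:
- value 5: 29/7 = 4.14, score 0.79
- value 5.5: 30.5/7 = 4.36, score 0.84
- value 6: 32/7 = 4.57, score 0.89

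A week of exactly 5 every day scores 1.00 under all three values.

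**Daily outcome of objective 1.1.b.** Assumptions not in the article: within-person daily SD of 1, 1.5 or 2 servings, and an open-category value of 5, 5.5 or 6. For each setting, 60,000 seven-day weeks were simulated with gamma-distributed daily intake rounded to half servings. The table shows the recorded change for a true rise of 1.0.

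| True rise | SD | Value 5 | Value 5.5 | Value 6 |
|---|---|---|---|---|
| 2 to 3 | 1 | 0.985 | 0.994 | 1.004 |
| 2 to 3 | 1.5 | 0.953 | 0.975 | 0.996 |
| 2 to 3 | 2 | 0.925 | 0.952 | 0.980 |
| 3 to 4 | 1 | 0.919 | 0.962 | 1.006 |
| 3 to 4 | 1.5 | 0.849 | 0.902 | 0.955 |
| 3 to 4 | 2 | 0.806 | 0.858 | 0.910 |
| 4 to 5 | 1 | 0.706 | 0.838 | 0.970 |
| 4 to 5 | 1.5 | 0.669 | 0.772 | 0.876 |
| 4 to 5 | 2 | 0.653 | 0.736 | 0.820 |
| 5 to 6 | 1 | 0.328 | 0.524 | 0.719 |
| 5 to 6 | 1.5 | 0.396 | 0.534 | 0.671 |
| 5 to 6 | 2 | 0.438 | 0.543 | 0.648 |

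Repeating this with normal daily intake widens the ranges a little. Over both shapes, a rise from 4 to 5 is recorded as 0.59-0.71, 0.68-0.84 or 0.77-0.98, and a rise from 5 to 6 as 0.31-0.44, 0.49-0.54 or 0.59-0.72. At a true mean of 5, 38-45% of days fall in the open category.

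No single value repairs this. With an SD of only 0.5, a value of 6 records a rise from 4 to 5 as 1.105, an overstatement.

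**Index.** By design "the environmentally sustainable healthy diet index will range from 0 to 10 points", and this item supplies at most 1 point. For a rise from 4 to 5 at SD 1, 1.5 and 2, the item gains 0.212, 0.197 and 0.186 point without a ceiling. With the least favourable value, 5, it gains 0.177, 0.167 and 0.163. The losses are 0.035, 0.030 and 0.023, and at most about 0.04 with normal intake. For a rise from 4 to 6 at SD 1.5, the gain is 0.998 - 0.746 = 0.252 without a ceiling and 0.952 - 0.685 = 0.267 with value 5, so nothing is lost.

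**The case against.** Several counterarguments have weight.

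- **Starting level.** The article gives no baseline intake. Its power simulation implies mean index values of 6 - 2 = 4, then 6, then 6 + 2 = 8. If this item scored like the average item (an assumption), the corresponding intakes would be 1 + 4 x 0.4 = 2.6, 3.4 and 4.2 servings a day. At SD 1.5 and value 5.5, a rise from 2 to 3 then loses about 2-3% and a rise from 3 to 4 about 10%. This stands. The problem is serious only for participants who come near 5.
- **Analysis-plan detail.** The value of the open category and any censoring method may be set in an analysis plan that is not shown, so their absence is not held against the article. But a later plan cannot recover amounts the app never recorded, and the answer list is fixed here.
- **Brevity and pilot status.** One short uniform list suits daily use, and the authors intend to use these data to refine the tool and examine its sensitivity to change. That explains the choice. It also makes a ceiling at the target relevant to the pilot's own aims.
- **Changing a running study.** The study started in October 2022 and compares phases within participants. Lengthening the list partway through a participant's year would mix a change of instrument with the change of phase. This stands and limits the fix.

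A reader might also infer that improvement is lost from the index, or that participants averaging 5 a day are scored as failing the target. The documents do not support either reading. Scoring is proportional, the index gives no credit above a mean of 5 by design, and no planned analysis uses whether the full point was earned.

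**Conclusion.** The point holds for the daily fruit and vegetable outcome of objective 1.1.b. The bias is an attenuation: the effect is reduced but does not disappear. It is small for a rise from 2 to 3 servings a day (mostly under 10%) and moderate from 3 to 4 (up to about 19% in the table, at SD 2 and value 5). From 4 to 5 it ranges from almost nothing (value 6, SD 1) to about 40% (value 5, SD 2, normal intake). From 5 to 6, roughly 30% to 70% of the change goes unrecorded. These sizes depend on the assumed daily SD, the assumed value of the open category and where participants start, none of which the article states. That the list cannot distinguish days above 5 does not depend on any of them.

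The effect on the diet index is minor: at most about 0.04 of 10 points for a rise from 4 to 5, against the 2 points per phase assumed in the power simulation. This is a worthwhile, inexpensive improvement to one specific outcome and does not threaten the main index analysis.

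**What to change.** For participants not yet assessed, extend the answer list of the fruit and vegetable item only, for example half servings up to 10 or numeric entry. Do so before the first baseline assessment, so that the scale is identical in all three phases.

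For participants already assessed with the present list, keep it unchanged to the end. Analyse their daily fruit and vegetable outcome with a mixed model that treats open-category days as right-censored at 5, at least as a sensitivity analysis beside the planned linear model. State the value given to the open category wherever daily values are averaged or modelled without censoring.

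The cost is a slightly longer list for one item and one additional model, with no extra assessment. If both lists end up in use across participants, report which participants used which. Switching a participant between lists should be avoided.
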